## Abstract

**Background:**

The high number of involuntary placements of people with mental disorders in Switzerland and other European countries constitutes a major public health issue. In view of the ethical and personal relevance of compulsory admission for the patients concerned and given the far-reaching effects in terms of health care costs, innovative interventions to improve the current situation are much needed. A number of promising approaches to prevent involuntary placements have been proposed that target continuity of care by increasing self-management skills of patients. However, the effectiveness of such interventions in terms of more robust criteria (e.g., admission rates) has not been sufficiently analysed in larger study samples. The current study aims to evaluate an intervention programme for patients at high risk of compulsory admission to psychiatric hospitals. Effectiveness will be assessed in terms of a reduced number of psychiatric hospitalisations and days of inpatient care in connection with involuntary psychiatric admissions as well as in terms of cost-containment in inpatient mental health care. The intervention furthermore intends to reduce the degree of patients’ perceived coercion and to increase patient satisfaction, their quality of life and empowerment.

**Methods/Design:**

This paper describes the design of a randomised controlled intervention study conducted currently at four psychiatric hospitals in the Canton of Zurich. The intervention programme consists of individualised psycho-education focusing on behaviours prior to and during illness-related crisis, the distribution of a crisis card and, after inpatient admission, a 24-month preventive monitoring of individual risk factors for compulsory re-admission to hospital. All measures are provided by a mental health care worker who maintains permanent contact to the patient over the course of the study. In order to prove its effectiveness the intervention programme will be compared with standard care procedures (control group). 200 patients each will be assigned to the intervention group or to the control group. Detailed follow-up assessments of service use, psychopathology and patient perceptions are scheduled 12 and 24 months after discharge.

**Discussion:**

Innovative interventions have to be established to prevent patients with mental disorders from undergoing the experience of compulsory admission and, with regard to society as a whole, to reduce the costs of health care (and detention). The current study will allow for a prospective analysis of the effectiveness of an intervention programme, providing insight into processes and factors that determine involuntary placement.

**Trial registration:**

Current Controlled Trials ISRCTN63162737.

## Background

Compulsory admission and use of coercive measures are accepted as necessary (and justified by the laws of most countries) in certain situations in clinical psychiatry: Compulsory admission is mandatory in cases of considerable danger to oneself or to others due to psychiatric illness. Notwithstanding that compulsory admission is regarded as indispensable to cope with violence and to prevent possible physical and psychological damage to the patient and/or others, the use and potential misuse of coercion in psychiatry has been accompanied for quite some time by critical debate [1]. A major argument in this debate is that coercive measures affect a patient’s personal interests profoundly: They constitute not only a serious restriction of a person’s freedom, but may also be perceived by a patient as unjustified or harmful [2]. Moreover, coercion may have adverse effects on the therapist-patient relationship and be associated with negative outcomes [3].

Beyond the ethical and personal relevance for the patients concerned, compulsory admission of people with mental disorder has far-reaching effects also in terms of health care costs. In most medical fields today, a primary aim of health care strategies is to prevent inpatient treatment and to minimise the length of hospital stays without diminishing the quality of care for the patient. This applies particularly to chronic diseases where institutionalised care affects the life of the patients to a maximum, while at the same time significantly increasing the financial burden of the funding agencies.

The legal basis for compulsory admission in Switzerland is regulated by the Swiss Civil Code Art. ZGB 397a, but implementary regulations are on a Federal State (“cantonal”) level. Unlike in other countries, there is no involuntary outpatient commitment in Switzerland. According to Art. 397a ZGB “an adult or a ward of court may be committed to or detained in a suitable institution on account of mental illness, learning disabilities, alcoholism, addiction to other substances or serious self-neglect, provided there is no other way to ensure his personal welfare. Account must be taken of any strain the person places on those around him or her. The person in question must be released as soon as his condition allows” [4]. Decisions on committal are taken by the guardianship authority at the domicile of the person concerned or, where there is risk in delay, by the guardianship authority of the place where he is staying. In cases where there is risk in delay or the person is psychologically ill, the cantons may authorise other suitable bodies to take such decisions. In the Canton of Zurich, all physicians are authorised to mandate compulsory admission to psychiatric care.

According to international comparisons, the frequency of involuntary placement has increased in a number of European countries, whereas in most EU member states involuntary placement quotas have remained more or less stable [5]. Compared to other European countries, Switzerland has one of the highest rates of compulsory admission of people with mental disorder [6]: Of all inpatient psychiatric admissions in the Canton of Zurich, compulsory admissions accounted for more than 30% for many years (Austria 19%; Germany 15%; Portugal 3% [7]). This rate has declined to some extent in recent years, but is at a comparatively high level until today (23% in 2007; PSYREC [8]).

In Switzerland though there is no shortage of community services: In the Canton of Zurich community mental health services are provided by 12 psychiatric institutions, and a total of 579 psychiatrists in office practice serve a population of 1.3 million people [9]. Despite extensive health care resources, the treatments offered are obviously not optimally adapted to the needs of mentally ill people.

In light of the high use of involuntary placement the need for innovative interventions to improve the current situation has frequently been advocated. Various efforts have been directed to integrate mentally disordered patients into the complex system of mental health services: These efforts range from empowerment and psycho-education to preventive measures targeting the “continuity of care”, which are considered to be helpful to enhance compliance with psychiatric treatment programmes, thus resulting in a reduction of voluntary and involuntary inpatient episodes, costs and transfers of patients to the criminal justice system.

A recent study reported promising results of a trial implementing a form of *advance agreement*. In a sample of 160 participants with a diagnosis of psychotic or bipolar disorder, the use of a joint crisis plan that was formulated by the patient, care coordinator, psychiatrist and project worker resulted in a significant decrease in the number of compulsory admissions. The number of days during which the patient was compulsorily treated was reduced by half [10]. The intervention also proved to be cost-effective [11]. Since the study sample was recruited from community mental health teams and included only a small diagnostic spectrum, results can not necessarily be generalised to psychiatry patients. Negative effects in terms of subsequent readmissions and self-efficacy at follow-up, however, have been reported by Papageorgiou et al., who studied the effects of advance directives in a sample of 156 in-patients receiving compulsory psychiatric treatment [12].

Furthermore, psycho-educational programmes have been introduced into routine psychiatric treatment and can be considered as a quality standard in psychiatric care [13]. Undoubtedly valuable and indispensable measures, their effect with regard to the above-mentioned specific problems, however, seems to be limited. From the perspective of *health psychology* a promising approach to prevent involuntary placement stresses the patient’s own interest to avert losing autonomy. This concept proposed by Krischke [14] suggests psycho-education focused on individual risk factors for crises and close monitoring by a personal mental health care worker in order to detect early signs of a crisis or threatening relapse, thus offering opportunities to react adequately and timely. A prerequisite of such an approach is the availability of crisis centres within the system of community mental health services which patients can contact in case of a threatening relapse.

Another concept originating in the voluntary sector as an advocacy tool for use in mental health emergencies is that of C*risis Cards*[15]. Crisis cards allow patients to state how they wish to be treated in a mental health emergency, during which they may have difficulties in making their wishes known. A crisis card may provide information about contact persons the patient knows and trusts, current treatments or treatments that have proved helpful or unhelpful in the past, or any medication the patient is currently taking.

Although the topic is of high relevance for the patients concerned as well as for health care policy, to date there is only preliminary research in this field. Effects in terms of more robust effectiveness criteria (e.g. significant reduction of admission rates, cost-effectiveness) have been investigated in larger study samples only lately:

A randomised controlled trial, CRIMSON, is currently conducted in Great Britain [16]. This trial aims to determine whether joint crisis plans, compared with treatment as usual, are effective in reducing the proportion of mental-health-service-users treated or detained under UK’s Mental Health act and will lead to improvement in total cost of care provision as well as further secondary outcomes. Eligible service users are people with a history of relapsing psychotic illness.

A further ongoing randomised controlled trial in the Netherlands aims to study the differential effect of two types of crisis plans (a crisis plan facilitated through the patient’s advocate, or through the clinician), compared to a control condition [17]. This study investigates effects on the number of psychiatric emergency visits and (involuntary) admissions and on social and psychological functioning in adult outpatients with psychotic or bipolar disorder. Moreover, it addresses the mediating mechanisms responsible for possible effects, such as the quality of the therapeutic alliance, therapy adherence, self-efficacy and insight into illness.

A randomised controlled trial with a similar design as the study described in this paper was just finished at Central Institute of Mental Health Mannheim, Germany (PRÄVENT-study). However, no results were published to date. Due to the similar approach, findings of the PRÄVENT-Study and this study may be directly compared in the future.

The objective of the present study is to implement and analyse the effectiveness of a 24-month intervention programme aiming to prevent compulsory admission of mentally ill patients to psychiatric inpatient treatment and to reduce the length of stays in connection with involuntary inpatient episodes. The specific interventions include measures which are likely to increase the self-management skills of chronically ill patients or which may increase their treatment adherence or pharmacological drug compliance.

The study is implemented as a subproject within the framework of the *Zurich Programme for Sustainable Development of Mental Health Services* (ZInEP)*.* ZInEP, which is funded by a private donation, is settled in the interface between research and supply. It consists of six different subprojects, each covering a specific psychiatric research field. The new projects of supply ought to become reliable points of reference for the further development of the psychiatric supply in Switzerland as well as in Europe, and contribute to a sustainable quality improvement.

## Methods

### Aims

The study has three main goals:

1) To evaluate the effectiveness of an intervention that aims to prevent compulsory admission to psychiatric hospital treatment and to reduce the time in hospital in connection with compulsory inpatient episodes (primary outcome criterion)

2) To evaluate changes in the perspective of the patients, hypothesizing that the intervention changes patients’ perceived coercion so that they feel less coerced and increases patients’ empowerment, quality of life and treatment satisfaction (secondary outcome criteria)

3) To examine which characteristics on the patient level (treatment history, diagnosis, social network, treatment adherence in the two-year follow-up) modify the outcome.

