Additionally, individual risk factors for a potential crisis (e.g. familial, work or financial problems, accommodation etc.) and protective factors in case of a crisis (e.g. familial, social resources, behaviour etc.) are assessed. These risk and protective factors constitute an individual crisis guideline (check-list) to be discussed at the regular monitoring contacts during the follow-up period to predict signs of a crisis.

Psycho-educational instruction aims to increase the patients’ self-management skills, to enhance their overall treatment compliance and intake of psychopharmacologic drugs and to activate the patients’ potential for secondary prevention of relapses.

(b) Individualised crisis card

Based on the essential parts of the individual crisis guideline (a), a crisis card is drawn up in collaboration with the patient and handed out to the patient during the last instruction session. Crisis cards contain information on the patient, professional or personal contact persons, treatment, medication, and an individual action plan in case of a crisis or relapse.

Apart from collecting information and discussing the patient’s individual condition, this procedure deepens the relationship between patients and their personal mental health care workers and enhances the basis for trusting contacts during the follow-up. Moreover, it increases the patient’s feeling of being actively involved in his/her care. Accordingly, it is left to the patient to provide his/her regular therapist with a copy of the crisis card.

(c) Preventive monitoring of individual risk factors for compulsory re-admission to hospital

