#### Data analysis and statistical power

All major endpoints of the study will be compared between the intervention and the control group. Primary outcome of the study is the time in hospital accumulated over all involuntary inpatient stays during the 24 month period. This outcome criterion will be analysed in terms of both “time in hospital” and savings of health care budgets (“health care costs”).

As further endpoints of the study (secondary outcome criteria) changes in the perspective of the patients are assessed. Hypothesised benefits of the intervention are a reduction of institutionalised care and coercion. Lower levels of subjectively experienced coercion are supposed to be associated with a respective increase in quality of life, treatment satisfaction and level of empowerment.

To address the major research questions, the quantitative outcome data will be analysed for the whole trial across the four centres, using General Linear Models. T-tests for independent samples are applied primarily to test the comparability of the intervention and the control group. Analyses of covariance are performed to compare the intervention and the control group with respect to the primary outcome (time in hospital accumulated over all involuntary inpatient stays) and secondary outcomes (reduction in levels of subjectively experienced coercion; increase in quality of life, treatment satisfaction and level of empowerment). Age, gender, centre and other variables which show significant between-group differences are included in the GLM models as covariates. To examine which characteristics on the patient level (treatment history, diagnosis, social network, treatment adherence in the two-year follow-up) modify the outcome, we examine the effects of these variables on the outcomes of interest within the intervention group, applying regression analyses. The level of significance is set at 0.05, two-tailed.

The planned overall sample size across all centres is 400 patients, of which 200 each will be assigned to the intervention group or to the control group. So each centre is expected to contribute 100 patients (50 intervention group and 50 control group).

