A further general limitation relates to the fact that with such a programme only those factors that contribute to compulsory admission which are subject to the patient’s self management can be modified. Compulsory admission to a psychiatric hospital of course does not depend only on a patient’s clinical status and characteristics of his/her psychosocial background. Rather, service system aspects that determine referral or crisis intervention procedures might have a share in the use of involuntary placement. With the current intervention programme only risk factors that can be governed by the patients themselves might be reduced, whereas further steps would have to be taken in order to effect a change in service system aspects. The effectiveness of preventive measures focusing on compulsory admission so far has only rarely been studied in larger samples. A strong point of this study lies in the opportunity to conduct a prospective analysis using a controlled randomised design. In Switzerland, the number of compulsory admissions has remained at an exceedingly high level for a long time. This is an unacceptable situation which necessitates the testing and the analysis of interventions targeting the factors that might be amenable to change in order to reduce the rate of involuntary placements. The present study focuses on the continuity of care after discharge from psychiatric hospital, in particular on measures which may increase treatment adherence or pharmacological drug compliance. These measures, aiming at the activation of the patients’ potential for secondary prevention of relapses by increasing the self-management skills of chronically mentally ill patients, appear to be a new and innovative strategy to prevent involuntary inpatient episodes.

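### Aim 3 lists adherence during follow-up as an outcome modifier, but adherence is a programme target measured over the same 24 months as the outcome, so its regression slope cannot be read as an effect

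*Protocol article*

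**What the plan says.** The Aims section gives as the third main goal "To examine which characteristics on the patient level (treatment history, diagnosis, social network, treatment adherence in the two-year follow-up) modify the outcome". The section on data analysis and statistical power repeats the list and states the method: "we examine the effects of these variables on the outcomes of interest within the intervention group, applying regression analyses".

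The article also says three times that the programme is meant to change adherence:

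- The Background describes interventions "which may increase their treatment adherence or pharmacological drug compliance".
- The Intervention section says that psycho-education aims "to enhance their overall treatment compliance and intake of psychopharmacologic drugs".
- The reflections on limitations and strength describe a focus on continuity of care, "in particular on measures which may increase treatment adherence or pharmacological drug compliance".

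The outcome window is fixed in the analysis section: "Primary outcome of the study is the time in hospital accumulated over all involuntary inpatient stays during the 24 month period".

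**The concern.** An outcome modifier is normally a characteristic that exists before treatment starts. Treatment history, diagnosis and social network are known by the t0 assessment. Adherence over the two-year follow-up is not: it develops after randomisation, alongside the outcome, and the programme tries to move it. The article itself, describing a Dutch crisis-plan trial in the Background, counts therapy adherence among mediating mechanisms. Here the same construct is given a different role.

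At stake is the interpretation of one of the three main goals. A negative slope of involuntary days on adherence would be open to the reading that adherence keeps patients out of hospital, yet the same slope can arise when adherence does nothing.

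**Working it through.** **1. The plan's own figure.** The sample size does not depend on this point, but it reproduces. With CV 1.25, σ² = ln(1 + 1.25²) = 0.941 and σ = 0.970. The effect is δ = ln(33/25) = 0.278. Then n = 2 × (1.960 + 0.842)² × 0.941 / 0.278² ≈ 192 per group, or 193 with the noncentral t. The article states 193.

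**2. Role and timing side by side.**

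| Item in the Aim 3 list | When determined | Target of the programme? |
|---|---|---|
| Treatment history | before follow-up | no |
| Diagnosis | index episode | no |
| Social network | social support scale at t0 only (Table 1) | not stated |
| Adherence | during the 24-month follow-up | yes, stated three times |

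Predictor and outcome share one window, and no time order is stated for this regression. Three explanations fit the same negative slope: adherence prevents admission; a crisis or admission disrupts adherence; illness severity lowers adherence and raises involuntary days. The article does not mention the second. It is an inference from the shared window. The third needs no effect of admission on adherence at all.

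**3. How small a non-causal correlation is enough.** Take n = 200 (the intervention arm, complete data), two-sided α = 0.05, and Fisher's z with standard error 1/√197 = 0.0712. Significance is reached at about |r| = tanh(1.96 × 0.0712) = 0.14. The probability of a significant result is Φ(atanh|r| × √197 − 1.96). The correlations below are assumptions, and adherence has no effect on the outcome in any row.

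| Assumed source of correlation | r | By formula | Simulated (4,000 runs) |
|---|---|---|---|
| None | 0 | 5% | 4.9% |
| Severity, loadings +0.4 and −0.4 | −0.4 × 0.4 = −0.16 | Φ(0.31) = 62% | 61% |
| Outcome acts on adherence | −0.2 | Φ(0.89) = 81% | 81% |
| Outcome acts on adherence | −0.3 | Φ(2.38) = 99% | 99% |

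**4. A month-by-month illustration.** Simulate 200 patients over 24 monthly steps, with no effect of adherence on admission. Stays have mean 33 days and CV 1.25 (from the power section). Assumed, not in the documents: 0.35 compulsory admissions per year, and adherence lowered in the admission month and the next two. Regress 24-month days on 24-month adherence. Ranges reflect different assumed settings for the remaining inputs, such as baseline adherence.

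| Assumed drop after admission | p < 0.05 |
|---|---|
| none | 4–5% |
| 0.5 logit | 7–8% |
| 1 logit | 13–18% |
| 2 logits | 33–60% |

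If admission risk also differs between patients, the figures for 1 and 2 logits rise to 25% and 68% in one such setting. The spurious slope is of the order of 1 to 4 fewer days per 10 points of adherence. If admission instead raises recorded adherence by 1 to 2 logits, the spurious slope is positive and significant in 9–19%. These settings imply 0.35 × 2 × 33 = 23.1 involuntary days over 24 months, whereas the article gives 33 days as the mean during a 24-month period, so they are not calibrated to the trial.

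**5. The time-ordered alternative.** With first-year adherence against second-year days, rejection is 4–7% when severity does not drive both. When severity is assumed to affect both admission rate and adherence, the analysis adjusted for first-year days still rejects in about 21–55%, depending on the loadings.

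**The case against.** **The regression runs within one arm.** Every patient in it is assigned to the programme, so there is no treatment contrast for a mediator to distort. Nor can a single arm show modification of a treatment effect for any of the four variables. Both statements are correct. They limit the mediator argument to a matter of classification, but the direction problem remains. It would also survive adding the control arm or an interaction term, because adherence would still arise after randomisation.

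**An article leaves detail to the full protocol or analysis plan.** The definition, timing and lagging of adherence may well be specified there, and their absence here is no fault. The classification is different: it is stated in the Aims and again in the analysis section, where the wording is "treatment adherence in the two-year follow-up) modify the outcome, we examine the effects of these variables on the outcomes of interest". The Intervention section does use the language of possible association for the individual course-of-illness data, which is the right label, but the analysis section does not carry it over.

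**Stronger readings that the documents do not support.**

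- A reader might infer that Aim 3 is meant to decide who should be offered the programme. The remark about which patients might qualify closes the dropout analysis and does not refer to Aim 3.
- A reader might infer that the regression will tend to favour adherent patients. That requires admission to lower adherence, or severity to drive both. The article states neither, and an inpatient stay could instead raise recorded drug intake.
- A reader might infer that time ordering restores the nominal error rate. Step 5 shows that it does so only without shared severity.

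**Conclusion.** The point holds for Aim 3. Adherence during follow-up is misclassified as a patient characteristic that modifies the outcome, and the regression as described cannot identify the direction of any association it finds. This rests on the text alone: the two lists, the three statements of programme intent, and the shared 24-month window.

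The size is illustrative. False-positive rates of roughly 7–8% to 33–60%, against a nominal 5%, follow from assumed drops of 0.5 to 2 logits and an assumed 0.35 admissions per year. The magnitude and even the sign depend on inputs that the documents do not give. The correlation check makes the same case more simply: with 200 patients, a non-causal correlation of about 0.14 is enough for significance.

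The primary comparison, the secondary outcomes and the sample size are not affected. The change is worth making because it is cheap and concerns a stated main goal.

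**What to change.** 1. Restrict the Aim 3 modifiers to characteristics fixed before randomisation, and remove follow-up adherence from the list in both the Aims and the analysis section. For items measured at t0, such as social support, confirm that the measurement precedes randomisation: the article schedules baseline upon discharge and randomises before the instruction sessions.
2. Analyse adherence separately and in time order. Relate a stated adherence measure from discharge to t1 to involuntary days from t1 to t2, adjusting for involuntary days before t1 and for baseline severity (BPRS, CGI or GAF).
3. Derive the measure from the CSSRI-EU data on medication and outpatient contacts. Its definition must be written down: the instrument records drugs and doses taken, and Table 1 has no adherence row. If both arms are used, allow for the different collection schedules (continuous in the intervention group, every 3 months in the control group).
4. Report the result as an association or possible mediator, not as an effect or modification.

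The cost is a change of wording, one definition and one additional analysis, with no new data collection foreseen. Only second-year events contribute to the adherence analysis, so it is less precise. Time ordering removes reverse causation within the shared window, but the adjustment covers severity only as far as the baseline scales capture it, so residual confounding should be acknowledged.
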